### Sample size estimation

2.5

The sample size calculation is based on the between-group comparison of glaucoma detection rate, which is the main endpoint of this study. Assuming that the glaucoma detection rate in the routine screening arm would approximate the reported glaucoma prevalence [approximately 3.54% (1, 19)], and that the tiered screening arm, through an optimized screening pathway, would achieve an increased detection rate of 4.54%, corresponding to a difference in detection rate (*Δp*) of 1%. Using this comparison (tiered screening versus routine screening), with a two-sided significance level of α = 0.05 and statistical power of 1 − β = 0.80, the minimum required sample size is calculated to be 6,283 participants per arm. This computation was performed using G*Power (version 3.1.9.7), employing the module for two independent proportions based on Fisher’s exact test.

The sample size is further adjusted for the cluster randomized design by applying a design effect (DEFF). Unlike chronic conditions substantially influenced by behavioral or lifestyle factors, the prevalence of glaucoma is predominantly driven by non-modifiable risk factors such as age and genetic susceptibility. Consequently, between-cluster variation in glaucoma prevalence is expected to be minimal across communities with similar demographic structures. We therefore assumed an intracluster correlation coefficient (ICC) of 0.005 (20) and an average cluster size of 40 participants, which yielded a DEFF of 1.195, approximated as 1.20, resulting in an adjusted requirement of 7,540 participants per arm. In addition, factoring in an anticipated loss-to-follow-up rate of 20%, the final required sample size increases to 9,425 participants per group (totally 28,275 participants in three groups, with *k* = 1).

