Secondary outcome measures include comparative analyses of the cost-effectiveness of different screening strategies and the diagnostic accuracy of physician-based versus AI-assisted image interpretation in fundus photography for screening glaucoma. The comparison of diagnostic accuracy will be evaluated at the per-participant level and will include sensitivity and specificity, as well as AUC for each interpretation method.

The cost-effectiveness analysis will be conducted from a societal perspective to comprehensively evaluate the resources consumed and health outcomes generated by different screening strategies. The primary economic outcome is the incremental cost-effectiveness ratio (ICER), expressed as the incremental cost per additional glaucoma case detected (based on observed data within the study period), and the incremental cost per quality-adjusted life year (QALY) gained (based on long-term model extrapolation). Cost components will encompass screening-related expenses, including personnel, equipment, consumables, site costs, and AI-assisted interpretation fees; diagnostic confirmation costs following referral, such as OCT and automated perimetry; subsequent treatment and follow-up costs; and direct non-medical and indirect costs, including transportation expenses and productivity losses incurred by patients and their families. Health utility values will be measured prospectively among diagnosed patients during follow-up using the EQ-5D-5L instrument and converted to utility weights using the Chinese value set. Costs and effects within the study period will be obtained through actual data collection, whereas long-term outcomes will be evaluated using a Markov state-transition model simulating the natural history of glaucoma and the long-term trajectory following screening intervention. The model will employ a cycle length of 1 year and a lifetime horizon, and future costs and health outcomes will be discounted to present value at an annual rate of 3%. Uncertainty in the incremental analysis will be assessed through one-way sensitivity analyses and probabilistic sensitivity analysis, and cost-effectiveness acceptability curves will be generated to illustrate the probability that the tiered screening strategy is cost-effective across a range of willingness-to-pay thresholds.

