### Statistical analyses

2.9

All statistical analyses will be performed using SPSS V25.0 (IBM, United States) and R software. Continuous variables will be expressed as Mean ± Standard Deviation (SD) or Median with Interquartile Ranges (IQRs), depending on the data distribution, while categorical variables will be presented as frequencies and percentages. Descriptive statistics will be used to summarize the baseline characteristics of each cohort.

Given the cluster randomized design of this study, all between-group comparisons will account for clustering effects. The comparison of the glaucoma detection rate as the primary endpoint will be analyzed using generalized estimating equations (GEE). The GEE model will employ a binomial distribution family and a logit link function, with study group as a fixed effect and community as the clustering variable, adopting an exchangeable working correlation matrix to adjust for within-community correlation. Comparisons of sensitivity and specificity will similarly be conducted using GEE to correct standard errors and confidence intervals (CIs). Cox proportional hazards regression and logistic regression analyses will incorporate cluster as a clustering variable or random intercept to identify risk factors associated with glaucoma incidence. Pearson’s χ^2^ test is utilized only for preliminary comparisons without adjustment for clustering, and final conclusions will be based on results accounting for clustering effects. A two-sided *p* < 0.05 will be considered statistically significant.

For missing data, the pattern, frequency, and possible causes of missingness will first be described. Baseline characteristics of participants with and without complete data will be compared to assess the missing data mechanism (whether missing at random). Primary outcome analyses will be performed using multiply imputed datasets, with complete-case analysis serving as a sensitivity analysis. For participants lost to follow-up after screening, sensitivity analyses using inverse probability weighting will be conducted to evaluate the potential impact of attrition on the estimation of the primary outcomes.

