Additionally, the cost-effectiveness analysis will adopt ICER as the economic evaluation measure, with estimated CIs using nonparametric bootstrapping. The sensitivity, specificity, and AUC of physician-based versus AI-assisted image interpretation will be calculated and compared, and differences in AUC will be assessed by the DeLong test or bootstrapping.

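### The bootstrap confidence interval planned for the within-study ICER loses its meaning when the difference in cases detected is not clearly above zero; incremental net benefit should carry the uncertainty

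*Protocol article*

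**What the plan says.** Section 2.9 (Statistical analyses) of the protocol article fixes the measure and its interval: "the cost-effectiveness analysis will adopt ICER as the economic evaluation measure, with estimated CIs using nonparametric bootstrapping". It names neither the type of bootstrap interval nor the resampling unit.

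Section 2.6 (Follow-ups and outcome variables) gives the ICER two forms. The within-study form is "expressed as the incremental cost per additional glaucoma case detected", from observed data. The other is cost per QALY, from a lifetime Markov model. After the description of that model, the section adds: "Uncertainty in the incremental analysis will be assessed through one-way sensitivity analyses and probabilistic sensitivity analysis". It also says that "cost-effectiveness acceptability curves will be generated to illustrate the probability that the tiered screening strategy is cost-effective" over a range of willingness-to-pay thresholds.

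On clustering, section 2.9 states that "all between-group comparisons will account for clustering effects".

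**The concern.** An ICER is a cost difference divided by an effect difference, and its sign does not say which strategy is better. A positive value can mean more cases at more cost, or fewer cases at less cost. A negative value can mean that the tiered strategy dominates or that it is dominated. While nearly all replicates have a positive effect difference, larger values are worse and two limits make sense. Once replicates fall on both sides of zero, values near the crossing go to plus or minus infinity, and sorting them puts contradictory conclusions side by side.

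The design leaves the sign open for tiered versus routine screening. Under section 2.4 and Table 1, the whole routine arm has pressure measurement and fundus photography at baseline, year 3 and year 6. In the tiered arm only people classed as high-risk by questionnaire have them, but every year. Cases that the questionnaire misses lower detection in the tiered arm, while annual examination may raise it. The Discussion expects tiering to spare most residents the expensive examinations, so the sign of the cost difference is open too. Fewer cases at lower cost is a possible result, and there an ICER interval would mislead.

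A preliminary evaluation of cost-effectiveness is one of the two main objectives (section 2.1), so its headline interval should hold up in the less favourable outcomes as well.

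**Working it through.** **Inputs (section 2.5).** Detection 3.54% (routine) and 4.54% (tiered); two-sided alpha 0.05; power 0.80; ICC 0.005; 40 participants per cluster; 20% loss to follow-up.

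**Reproducing the plan's sample size.** The two-proportion formula gives 6,085 per arm without a continuity correction and 6,283 with it, which matches the stated figure. The design effect is 1 + 39 × 0.005 = 1.195, rounded to 1.20. Then 6,283 × 1.20 = 7,540; 7,540 / 0.80 = 9,425; and 3 × 9,425 = 28,275. All agree with the protocol.

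**Standard error of the denominator, 7,540 analysed per arm.**
- Ignoring clusters: √[(0.0354 × 0.9646 + 0.0454 × 0.9546) / 7,540] = 0.0032.
- With clusters: 0.0032 × √1.195 = 0.0035, that is 0.35 percentage points.

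**How often the denominator is not clear of zero.** For a true gain d with clustered standard error SE:
- chance that the 95% interval reaches zero or below = Φ(1.96 − d/SE);
- share of replicates at or below zero when the observed gain equals d = Φ(−d/SE).

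| True gain (points) | SE | Interval reaches zero or below | Replicates ≤ 0 if observed = true |
|---|---|---|---|
| 1.0 (planned) | 0.0035 | 19% | 0.2% |
| 0.5 (assumed) | 0.0034 | 69% | 7% |
| 0 (assumed) | 0.0033 | 97.5% | 50% |

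A beta-binomial simulation (188 clusters of 40 per arm, ICC 0.005, planned gain, 400 trials, 1,000 resamples of whole clusters) gave 20.5% in place of 19%.

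**What this does to the ICER interval.** The protocol gives no costs, so this is an illustration only. Assume a cost difference of 50 units per person (SD 100), cost and effect independent, and no clustering of costs. The standard error of the cost difference is 100 × √(2/7,540) = 1.63.
- Gain of 1.0 point: 95% percentile limits of about 2,900 to 15,900. This is usable.
- Gain of 0.3 point: about −150,000 to +165,000, with 20% of replicates at or below zero. This has no interpretation.

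**The same 0.3-point case as net benefit.** Incremental net benefit is λ × (effect difference) − (cost difference). Take λ = 50 / 0.01 = 5,000, the ICER at the planned gain. The estimate is 5,000 × 0.003 − 50 = −35. Its standard error is √[(5,000 × 0.0035)² + 1.63²] = 17.6, so the 95% interval is −69.4 to −0.6. It is finite and ordered from the same data.

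**Resampling unit.** If individuals were resampled, the standard error of the detection difference would be too small by 1 − 1/√1.195 = 8.5%. Coverage of a nominal 95% interval would be 2Φ(1.96/√1.195) − 1 = 92.7%. These figures concern the detection difference. Those for the ICER would also depend on the variance and ICC of costs, which are not given.

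**The case against.** The strongest reply is that the protocol already has a suitable tool. An acceptability curve gives, at each threshold, the probability that net benefit is positive, and it stays interpretable when the effect difference is near or below zero. This carries weight and softens the point. It does not remove it: the curves follow the Markov and QALY text, so their use for the within-study cost per case is not explicit, and they do not repair the ICER interval to which section 2.9 still commits.

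Second, the 19% is largely the planned type II error in another form (power 0.80), and the 69% rests on a gain that the protocol does not assume. Both statements are correct. The figures show how often the stated interval would be in difficulty; they are not a separate flaw in the sample size.

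Third, section 2.9 names no interval type, and the objection to percentile limits presumes one. That is fair. However, any pair of finite limits on the ICER scale meets the same difficulty once the denominator may be zero.

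Two stronger readings are tempting and are not supported. A reader might infer that the interval is undefined whenever a zero difference is possible. Percentiles can still be computed, and at an observed gain of 1 point only about 0.2% of replicates lie at or below zero. A reader might also infer that individuals will be resampled and clustering ignored. The text does not say so. A bootstrap of whole communities is also nonparametric, the rule that all between-group comparisons account for clustering stands in the same section, and the resampling unit is a detail commonly left to the analysis plan.

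**Conclusion.** The point holds in a limited form. For within-study cost per case detected, the interval named in section 2.9 is sound when the observed gain is near the planned 1 point. It has no ordered interpretation when a non-trivial share of replicates is at or below zero. For tiered versus routine screening, the 95% interval for the denominator reaches zero in about 19% of trials at the planned gain and about 69% at half of it.

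These figures rest on 7,540 analysed per arm, the protocol's ICC and cluster size, and a normal approximation; the 0.5-point gain and all costs are assumptions. Comparisons with the no-screening arm were not computed, because the protocol gives no detection rate for it. On clustering there is no error in the protocol, only a unit worth naming. The change is worth making because a better method is cheap and should be settled before the results show the direction of the differences.

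**What to change.** Amend the economic paragraph of section 2.9 and align section 2.6 with it:

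1. Report the within-study ICER as a point estimate, and give a confidence interval only when the detection difference is clearly non-zero (for example, when its cluster-adjusted 95% interval excludes zero).
2. Express uncertainty as incremental net monetary benefit with its confidence interval over the planned willingness-to-pay range.
3. State that the acceptability curves also cover cost per case detected.
4. As a clarification in line with the existing clustering rule, state that the bootstrap resamples whole communities within arm and keeps each participant's cost and effect paired.

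No new data are needed. The cost is a few lines of code and the choice of a willingness-to-pay range per case detected, which is less familiar than one per QALY and should be fixed in advance.

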All participants who enter the Tier 3 screening stage will undergo further examinations for definitive diagnosis, including standard automated perimetry for visual field testing, optical coherence tomography (OCT) imaging of retinal nerve fiber layer (RNFL) thickness, and gonioscopy to distinguish open-angle from angle-closure glaucoma. The final diagnosis will be made independently by two glaucoma specialists following a comprehensive review of all clinical data, with reference to internationally accepted diagnostic criteria for glaucoma, namely the presence of characteristic glaucomatous optic neuropathy with corresponding visual field defects, after excluding other ocular or neurological conditions that may cause optic neuropathy. Any diagnostic disagreement between the two specialists will be resolved by a third senior glaucoma expert who will make a final determination. To correct for verification bias, a random sample of 10% of participants who are screen-negative will also be recalled to undergo the same reference standard examination. Sensitivity and specificity of the two screening strategies will be calculated based on all screen-positive participants and the randomly selected screen-negative subset, with appropriate weighting to account for the sampling fraction.

The study is scheduled to begin patient enrollment in October 2025, with follow-up and final data collection expected to be completed in December 2032.

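### The correction for 10% verification of screen-negatives is not extended to the physician-versus-AI comparison, and the permitted DeLong test cannot apply it

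*Protocol article*

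**What the plan says.** Section 2.2 (Study design) sends all screen-positives to the Tier 3 examination. To deal with verification bias, it adds that "a random sample of 10% of participants who are screen-negative will also be recalled to undergo the same reference standard examination". It then says how the results are used: "Sensitivity and specificity of the two screening strategies will be calculated based on all screen-positive participants and the randomly selected screen-negative subset". The same sentence goes on to promise weights that allow for the 10% recall. Its object is the two screening strategies.

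The reader comparison is a secondary outcome in section 2.6, where "The comparison of diagnostic accuracy will be evaluated at the per-participant level". Section 2.9 (Statistical analyses) gives its method: "The sensitivity, specificity, and AUC of physician-based versus AI-assisted image interpretation will be calculated and compared". For the AUC it leaves a choice between two procedures: "differences in AUC will be assessed by the DeLong test or bootstrapping". Neither section mentions weights for this comparison.

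Three other statements bear on the point:

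- Section 2.9 says that "all between-group comparisons will account for clustering effects". It also uses GEE for comparisons of sensitivity and specificity, to correct standard errors and confidence intervals.
- Section 2.9 uses inverse probability weighting only as a sensitivity analysis for attrition.
- Sections 2.2 and 2.7 (item 3) call the specialist's image judgment the reference or gold standard where physician and AI disagree.

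**The concern.** The plan recognises that verifying a tenth of the negatives distorts accuracy, and it prescribes the remedy for one pair of estimates. The physician and AI estimates depend on the same verified participants if the Tier 3 diagnosis is the truth, yet the remedy is not extended to them. One of the two methods allowed for the AUC difference cannot apply it.

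Selection here also depends on the tests being compared. Both image readings, with arbitration of disagreements, feed the Tier 2 decision, and that decision determines who is verified with certainty and who with probability 0.1. An unweighted analysis therefore keeps nearly all of the readers' positives and few of their joint negatives.

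Evaluating the AI tool is a stated objective (section 2.1), and the Discussion looks to wider use and guidelines. The reported sensitivity, specificity and AUC of each reader would support those conclusions.

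**Working it through.** **Figures the plan gives.** There is no sample size or assumed accuracy for the reader comparison. The related figures in section 2.5 reproduce: design effect 1 + (40 − 1) × 0.005 = 1.195, rounded to 1.20; 6,283 × 1.20 = 7,540; 7,540 / 0.80 = 9,425 per arm. The recall fraction f = 0.10 is from section 2.2. All reader accuracies below are assumptions.

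**One test that alone decides verification.** Unweighted sensitivity is Se / [Se + f(1 − Se)] and unweighted specificity is f·Sp / [f·Sp + (1 − Sp)]. Prevalence cancels. With assumed Se = 0.80 and Sp = 0.90:

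- sensitivity 0.80 / (0.80 + 0.02) = 0.976
- specificity 0.09 / (0.09 + 0.10) = 0.474

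This is the extreme case.

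**Two readers with arbitration.** Assumed: physician 75%/95%, AI 85%/93% (sensitivity/specificity), joint misses 10% of cases, joint false positives 2% of non-cases, arbiter correct 85% of the time.

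*Cases.* Both positive 1 − 0.25 − 0.15 + 0.10 = 0.70; physician only 0.05; AI only 0.15.

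- A discordant case is verified with probability 0.85 + 0.15 × 0.1 = 0.865.
- Verified share: 0.70 + 0.20 × 0.865 + 0.10 × 0.1 = 0.883.
- Physician: (0.70 + 0.05 × 0.865) / 0.883 = 84% (true 75%).
- AI: (0.70 + 0.15 × 0.865) / 0.883 = 94% (true 85%).

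*Non-cases.* Both positive 0.02; physician only 0.03; AI only 0.05; both negative 0.90.

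- A discordant non-case is verified with probability 0.15 + 0.85 × 0.1 = 0.235.
- Verified share: 0.02 + 0.08 × 0.235 + 0.90 × 0.1 = 0.129.
- Physician: (0.09 + 0.05 × 0.235) / 0.1288 = 79% (true 95%).
- AI: (0.09 + 0.03 × 0.235) / 0.1288 = 75% (true 93%).

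*With weights 1 and 10.* Physician specificity becomes 0.90 × 0.1 × 10 + 0.05 × (0.15 + 0.85 × 0.1 × 10) = 0.90 + 0.05 = 0.95, the true value.

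**Verification for other reasons.** Suppose 5% of non-cases are IOP-positive whatever the image shows (assumed).

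- A joint negative is verified with probability 0.05 + 0.95 × 0.1 = 0.145, and a discordant non-case with 0.15 + 0.85 × 0.145 = 0.273.
- Verified share: 0.02 + 0.08 × 0.273 + 0.90 × 0.145 = 0.172.
- Unweighted specificity becomes about 84% (physician) and 80% (AI). The distortion is smaller but remains.

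**AUC, by simulation.** Inputs: 3 million people, prevalence 3.54%, two correlated normal scores. Under adjudication the arbiter is positive in 85% of discordant cases and 5% of discordant non-cases.

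- Specificity 0.90, correlation 0.5, true AUCs 0.948 and 0.911 (difference 0.037). Unweighted: 0.894 and 0.815 (difference 0.079) if either positive reading leads to verification; 0.911 and 0.852 (difference 0.059) if disagreements are adjudicated. Weighted: 0.949 and 0.911 to 0.912.
- Same specificity and correlation, true AUCs equal at about 0.921. Unweighted: both 0.846 (either positive) or 0.875 and 0.874 (adjudicated). Each AUC falls, but the difference stays near zero.
- Mildest setting (specificity 0.95, correlation 0.3, adjudicated): 0.949 and 0.911 become 0.947 and 0.903. Specificity still appears as 0.88.
- Across the specificity-0.90 settings: specificity appears as 0.58 to 0.69, sensitivity rises by 0.06 to 0.11, and AUC falls by 0.03 to 0.12.

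**Clustering.** At the plan's ICC the standard error is understated by a factor of at most √1.195 = 1.09 with all 40 in a cluster analysed. If 10% to 30% of each cluster is verified (4 to 12 people), the factor is √(1 + 3 × 0.005) = 1.01 to √(1 + 11 × 0.005) = 1.03. The estimate itself does not move.

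**The case against.** The strongest reply is that this is silence in a condensed article. Section 2.9 nowhere says that verified participants get equal weight or are treated as independent, and a fuller analysis plan could supply the weights. A reader might infer that the reader results will be badly biased; the documents do not support that. Bootstrapping is named beside DeLong, and nothing prevents a weighted bootstrap that resamples communities. What stands against this reply is that the article does more than stay silent: it limits its correction to the strategies and names, as an acceptable option, a test that in standard form cannot apply it.

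A reader might also infer that clustering biases the comparison, or that the 10% sample is drawn by community. Neither is supported. Community is the unit of randomisation (section 2.4), while the recall is a random sample of participants. The GEE sentence can be read to cover reader sensitivity and specificity, and clustering affects only the standard error. GEE does not, however, remove selection from verification.

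The reference standard is a fair objection. If the adjudicated image reading is the truth for this comparison, partial verification is not the main problem. Another problem then appears: specialist judgment is described only for disagreements, so if agreed readings are taken as correct, glaucoma missed by both readers leaves the denominator. Under the assumptions above and a perfect arbiter, that effect alone gives 0.75 / 0.90 = 83% and 0.85 / 0.90 = 94% instead of 75% and 85%.

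The size also rests on assumed figures. In one further simulation with nearly equal true AUCs (0.898 and 0.899), the unweighted values were 0.880 and 0.874, so the difference moved only from +0.001 to −0.006. Positives on IOP or other tests reduce the distortion further.

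**Conclusion.** The point holds conditionally. The plan does not secure for the reader comparison the verification correction that it applies to the screening strategies, and it permits a test that cannot carry it. No other statement in section 2.9 closes the gap.

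If the Tier 3 diagnosis is the reference and the analysis is unweighted, specificity is affected most: 7 to 32 percentage points too low across the two-reader settings above. Sensitivity is roughly 6 to 12 points too high. The effect on AUC runs from under 0.01 to about 0.12. A real difference between readers is widened in the simulated settings, while two equally accurate readers with equal specificity show almost no spurious difference. These sizes depend on reader accuracy, reader correlation, arbiter accuracy and the share verified for non-image reasons, none of which the protocol gives.

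Clustering is a minor standard-error matter, at most about 9%. The comparison is a secondary outcome, so the detection-rate endpoint is not touched. The change is still worth making before results are seen, because the choice between DeLong and a weighted bootstrap could alter the conclusion about the AI tool.

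**What to change.** In section 2.9:

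1. State that the reader comparison uses the Tier 3 comprehensive examination as reference standard, not the adjudicated image reading described in sections 2.2 and 2.7.
2. Weight reader sensitivity, specificity and AUC by the inverse of the verification probability: 1 for verified screen-positives, 10 for recalled screen-negatives.
3. Replace the DeLong option with a paired, weighted bootstrap that resamples communities and keeps both readings of a participant together. This also settles the clustering point.

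The cost is a few sentences and a short program, with no extra data. Intervals will be somewhat wider than DeLong would show.
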